### MRI data preprocessing

Preprocessing of MRI images will be conducted using the DPARSF (http://rfmri.org) and SPM 12 (www.fil.ion.ucl.ac.uk/spm) toolkits within MATLAB 2014b (MathWorks, Natick, MA). The preprocessing pipeline will include the following steps: (1) removal of the first 10 volumes; (2) slice timing correction; (3) realignment of images to correct for head motion; (4) co-registration of T1-weighted images with functional images; (5) normalization of T1 images to Montreal Neurological Institute (MNI) space, followed by segmentation into gray matter, white matter, and cerebrospinal fluid; (6) spatial smoothing of the images using an isotropic Gaussian kernel with a full width at half maximum (FWHM) of 6 mm; (7) temporal bandpass filtering (0.01-0.08 Hz); and (8) regression of nuisance signals, including global mean, white matter, cerebrospinal fluid signals, and six motion parameters. Considering the aim is to estimate the relationship between ovarian and brain and the hypothalamic-pituitary-ovarian (HPO) axis, the region of interest (ROI) will be selected as the hypothalamus. For static functional connectivity (FC) analysis, Pearson’s correlation coefficients between the reference time series of each seed and the time series of all brain voxels will be computed. These coefficients will then be transformed into z-scores using Fisher’s z-transformation to enhance normality (24). Two-sample t-tests will be conducted to identify significant differences in FC between the DOR and healthy control (HC) groups, with age and mean framewise displacement (FD) as covariates. Moreover, Kisspeptin is a key regulator of gonadotropin secretion and is primarily located in the rostral preoptic area and the infundibular nucleus of the human hypothalamus (37). In this study, we will refer to the segmentation method described in Ogawa (38) to perform subregion segmentation of the hypothalamus in our subjects, with a particular focus on the rostral preoptic area and the infundibular nucleus, as well as the whole-brain FC. For the longitudinal analysis, paired t-tests will be used to compare within-group statistical maps, while a two-way analysis of variance (ANOVA) will be applied to compare between-group statistical maps. Multiple comparisons will be corrected for using a threshold of *p* < 0.05 at the voxel level and *p* < 0.05 at the cluster level, with false discovery rate (FDR) correction.

A conjunction analysis will be performed to investigate whether the altered hypothalamic functional connectivity (FC) in DOR patients is influenced by acupuncture treatment. This analysis will compare the FC change maps in DOR patients with the treatment effects observed in the VA and SA groups, respectively. Additionally, to examine the relationship between clinical outcomes and FC changes, correlation analyses will be conducted between the significantly altered hypothalamus-related FCs and the corresponding clinical improvements in the VA group.

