### fMRI data acquisition

All DOR patients received two separate resting-state fMRI scanning, before and after the 12 weeks acupuncture treatment course, respectively. The healthy controls participated only in one resting-state scanning as baseline control. For all participants, fMRI scanning should be done at least 3 day away from their menstrual period.

In this study, 3.0 T MRI scanner (Siemens, Sonata, Germany) at the Sir Run Shaw Hospital, was used to perform cranial scans on all subjects. (1) T1-weighted imaging (T1WI): horizontal axis position, TR = 600 ms, TE = 10 ms, slice thickness = 4 mm, slice gap = 1.5 mm, field-of-view (FOV) = 240 mm × 240 mm, matrix = 256×256. (2) Resting-state fMRI sequence and parameters: acquired with gradient echo-echo planar imaging (GRE-EPI) sequence, TR = 2000 ms, TE = 30 ms, slice thickness = 4 mm, slice gap = 1.2 mm, FOV = 220 mm × 220 mm, matrix = 64 × 64, flip angle = 90°, 200 time points in total, 35 slices scanned continuously. The entire brain will be scanned, and during the procedure, participants will be instructed to lie supine with their eyes open, while being asked to refrain from focusing on any specific thoughts.

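### Band-passing the images before regressing motion parameters not stated to be filtered, and smoothing before the seeds are read, can leave motion in the connectivity maps and blur small hypothalamic seeds

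*Protocol article*

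**What the plan says.** The protocol article numbers its preprocessing steps under MRI data preprocessing. Those that matter here are:

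- "3) realignment of images to correct for head motion", which is where the motion parameters are estimated;
- "6) spatial smoothing of the images using an isotropic Gaussian kernel with a full width at half maximum (FWHM) of 6 mm";
- at step 7, a band-pass of the images that keeps fluctuations between 0.01 and 0.08 Hz;
- "8) regression of nuisance signals, including global mean, white matter, cerebrospinal fluid signals, and six motion parameters".

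Seed-to-voxel Pearson correlations are described after these steps. The seed is the hypothalamus, with special attention to two subregions, the rostral preoptic area and the infundibular nucleus, whose sizes are not given. The text does not say whether the motion parameters are band-passed, and it mentions no separate unsmoothed data set for the seed or tissue signals. Age and mean framewise displacement (FD) are covariates in the DOR versus healthy control comparison. No FD covariate is stated for the paired t-tests or the ANOVA.

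Under fMRI data acquisition, the resting-state images have "slice thickness = 4 mm, slice gap = 1.2 mm, FOV = 220 mm × 220 mm, matrix = 64 × 64" and "200 time points in total, 35 slices scanned continuously", with a repetition time of 2 s.

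**The concern.** Two separate things can go wrong with this sequence.

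**Motion.** Once the images are band-passed, they hold only 0.01-0.08 Hz fluctuations. A raw motion parameter also varies outside that band. Least squares then gives it too small a coefficient, so part of the in-band motion stays. The fitted term also carries out-of-band motion, which is subtracted from data that no longer contain it and so reappears as noise. Voxels that share residual motion look connected.

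**Blur.** Smoothing first mixes a small seed with its neighbours, and mixes white matter and CSF with grey matter, before any of these series is read.

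Hypothalamic connectivity is the mechanistic outcome of the study. The conjunction analysis and the correlations with clinical change inherit any artefact in the maps.

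**Working it through.** The article states no figure that depends on the step order, so there is nothing of its own to reproduce.

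**Inputs from the article.** 200 - 10 = 190 volumes; repetition time 2 s; band 0.01-0.08 Hz; six motion parameters; 6 mm FWHM; in-plane voxel 220/64 = 3.44 mm; slice spacing 4 + 1.2 = 5.2 mm.

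**Assumptions.** Motion spectrum and amplitude; seed size and shape.

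**Motion, algebra for one regressor.** Let f be the share of the regressor's variance inside the band. Regressing filtered motion on raw motion gives a coefficient of f. As fractions of the in-band motion variance:

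- in-band motion left: (1 - f)²;
- out-of-band noise added: f(1 - f);
- total: 1 - f.

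For white motion the simulated f is 0.287. This gives 0.713² = 0.51 left in band, 0.287 × 0.713 = 0.20 added back, and 0.71 in total.

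**Motion, simulation with six raw regressors.**

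- In-band motion variance left: 49% (white), 36-38% (drifting), 14% (AR 0.7).
- Total left when the added out-of-band noise is counted too: 69%, 50% and 52% for spectra 1/f⁰, 1/f¹ and 1/f². The two sets measure different things and do not conflict.
- Spurious correlation between two otherwise unrelated series, with motion SD equal to signal SD: 0.32, 0.35 and 0.21 for the same three spectra, against 0.40, 0.50 and 0.34 with no regression. Runs with other motion models gave 0.15-0.26 and 0.29-0.44.
- After regressing before filtering, or filtering the regressors with the same band: about 0 (-0.003 to 0.006).

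**Blur.** Kernel sigma = 6/2.355 = 2.55 mm. At the centre of a cubic seed of side s, the share of signal from inside the seed is (2Φ(s/(2 × 2.55)) - 1)³. For spherical seeds of diameter s, the share of the seed-mean signal was found by Monte Carlo.

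| s (mm, assumed) | Cube centre, smoothing only | Sphere mean, smoothing only | Sphere mean, voxel only | Sphere mean, both |
|---|---|---|---|---|
| 3 | 9% | 4.5% | 20% | 3% |
| 4 | 18% | 9% | 34% | 7% |
| 5 | 31% | 15% | 45% | 12% |
| 6 | - | 22% | 53% | 18% |
| 8 | - | 34% | 64% | 30% |
| 10 | - | 44% | 71% | 40% |

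The sampled voxel including the gap is 3.4375² × 5.2 = 61.4 mm³. Cubic seeds of 3, 4 and 5 mm therefore fill 27/61.4 = 0.4, 64/61.4 = 1.0 and 125/61.4 = 2.0 voxels. Reading the seed from unsmoothed data moves the share from the last column to the one before it: from 3-12% to 20-45% at 3-5 mm.

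**The case against.** **The text is silent on filtering the regressors.** A reader might infer from the order alone that motion stays in the maps. The article does not support that. If the six parameters are band-passed identically, the printed order leaves about none. White matter, CSF and global signals taken from the filtered images would already be band-limited. A condensed article may leave this detail to a fuller document. This objection stands, and it makes the motion half conditional. What remains is that the article prints a sequence that is sound only under a condition it does not state.

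**Other safeguards are stated.** Mean FD is a covariate for DOR versus healthy controls, which addresses a group difference in motion there, although it does not clean each map. No such covariate is stated for the longitudinal comparisons. Step 8 also removes the global mean, which the simulations above leave out. When it was added, with raw motion parameters and in-band motion SD equal to signal, the spurious correlation fell from 0.33-0.42 to between -0.03 and 0.00 if the two voxels' motion pattern matched the global one. It fell to 0.07-0.11 at a pattern correlation of 0.9 and to 0.26-0.33 at 0.5, and did not fall at 0. The simulated correlations are therefore not estimates for this trial.

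**Seed sizes are assumed, and the segmentation method is only cited.** Both are true. The loss is nevertheless large over the whole 3-10 mm range.

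**Reordering does not cure the blur.** This is also true: the voxel-size part remains.

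**Conclusion.** The point holds in a conditional form and should be addressed.

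- **Motion.** If the motion parameters enter step 8 unfiltered, about 14-49% of in-band motion variance remains under the spectra tried, and out-of-band noise is added. How much spurious connectivity follows in this trial cannot be stated. It depends on the amplitude and spectrum of motion, on how far global-signal regression absorbs it and, for DOR versus healthy controls only, on the FD covariate.
- **Blur.** As printed, smoothing precedes reading of the seeds. For assumed seeds of 3-5 mm, about 5-30% of the signal comes from inside the seed, before voxel blur.

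A reader might go further and conclude that the acquisition must change or that the subregion seeds must be dropped. The documents do not support this:

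- Removing the slice gap would cut coverage from 35 × 4 + 34 × 1.2 = 180.8 mm to 35 × 4 = 140 mm, while the article requires the whole brain to be scanned.
- The structural scan has "slice thickness = 4 mm, slice gap = 1.5 mm", but its in-plane resolution is 240/256 = 0.94 mm. How far the cited segmentation depends on this scan cannot be seen.
- The subregions are a stated aim of a study that calls itself exploratory.

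These are trade-offs for the investigators, not corrections.

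**What to change.** 1. Run the nuisance regression before the band-pass, with all regressors taken from unfiltered data. Alternatively, keep the order and state that every regressor, including the six motion parameters, receives the identical 0.01-0.08 Hz filter.
2. Extract the seed, white matter and CSF series from unsmoothed images. Use smoothed data only for the target voxels or the resulting maps. Put the seed series through the same regression and filter as the target voxels.
3. State that conclusions about the rostral preoptic area and infundibular nucleus are exploratory and limited in spatial specificity, because sampling at 3.44 × 3.44 × 5.2 mm leaves blur after step 2.

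**Cost.** Items 1 and 2 change the processing scripts and a few lines of text. They need no new scans or participants. Item 3 costs only a narrower claim about the subregions.

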## Materials and methods

### Study design

This study will consist of two experiments: a cross-sectional experiment and a longitudinal experiment (**Figure 1**). The cross-sectional experiment will examine brain functional connectivity (FC) in patients with DOR by comparing seed-based FC between DOR patients and healthy controls (HCs). The longitudinal experiment will investigate the clinical efficacy of acupuncture and its underlying neurological mechanisms by comparing FC before and after treatment. Additionally, we will compare the differences in FC and clinical symptoms, such as ovarian function, anxiety, depression, and sleep disturbances, between the VA and SA groups following treatment. Finally, we plan to analyze the relationship between changes in FC and clinical symptoms. This will allow us to investigate whether acupuncture can modulate hypothalamic FC and subsequently improve clinical symptoms in DOR patients. The longitudinal acupuncture experiment was approved by the Ethics Committee of Sir Run Shaw Hospital Zhejiang University School of Medicine (2025YL0012) and submitted to the International Traditional Medicine Clinical Trial Registry (ITMCTR2025000576). All participants will be provided written informed consent before the initiation of any study procedures. The study adhered to the CONSORT guidelines for reporting

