### Acupuncture interventions

Eligible participants will be randomly allocated into the VA or SA group at a 1:1 ratio via the web-based response system of the Central Randomisation System for Clinical Research. Stratified randomization will be applied, with age (35 years) as the stratification factor. Unblinding will not be required during the study as it will not have clinical relevance to treatment decisions. The randomization plan will be generated using the “Proc plan” procedure in SAS 9.3 statistical software (SAS Institute Inc., Cary, NC, USA), and all related parameters set during the randomization process will be stored in a blinded database. When eligible participants are enrolled, the randomization number will be assigned by the responsible personnel or researcher through phone or online access to the central randomization system. The random distribution cards will contain random numbers, serial numbers, and groups, packed in opaque numbered envelopes. The envelope will be unsealed following study enrolment. Owing to the particularity of acupuncture research, it is difficult to blind the acupuncture operators. As such, fake acupuncture devices and separate treatment rooms will be used for each patient to blind them as much as possible. Moreover, the “three separations strategy” will be strictly adhered to by researchers, operators, and statisticians throughout the research process. Efficacy evaluation, data analysis, and statistics will be completed by third parties blinded to the groupings.

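### Mean FD is a covariate in the DOR–HC map but is not named for the longitudinal maps, so a motion shift between scans can pass for an FC change within an arm

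*Protocol article*

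**What the plan says.** All of this is in the Protocol article.

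- **Subject-level motion handling, every scan** (MRI data preprocessing): the pipeline includes "realignment of images to correct for head motion" and "regression of nuisance signals, including global mean, white matter, cerebrospinal fluid signals, and six motion parameters".
- **Cross-sectional map** (same section): the DOR–HC two-sample t-tests are run "with age and mean framewise displacement (FD) as covariates".
- **Longitudinal maps** (same section): "paired t-tests will be used to compare within-group statistical maps, while a two-way analysis of variance (ANOVA) will be applied to compare between-group statistical maps". No covariate is attached to either model, and no other section adds one or sets an FD limit for these scans.
- **Threshold, FDR-corrected** (same section): "Multiple comparisons will be corrected for using a threshold of *p* < 0.05 at the voxel level and *p* < 0.05 at the cluster level".
- **Scans** (fMRI data acquisition): "All DOR patients received two separate resting-state fMRI scanning, before and after the 12 weeks acupuncture treatment course, respectively".
- **Allocation** (Acupuncture interventions): "Eligible participants will be randomly allocated into the VA or SA group at a 1:1 ratio", stratified by age.
- **Use of the maps**: Study design says the longitudinal experiment will study "underlying neurological mechanisms by comparing FC before and after treatment". The paragraph after MRI data preprocessing sets the DOR map against the VA and SA treatment effects separately. It then correlates altered hypothalamic FC with clinical improvement in the VA group alone.

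**The concern.** Adjusting the DOR–HC map for mean FD, after realignment and motion regression have already been applied, treats residual motion as a possible confounder of FC. The same preprocessing is applied to the longitudinal scans, so the same residual could be present there.

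Leaving age out of the longitudinal models is harmless: it is practically constant within a patient and is the stratification factor. Mean FD is different because each patient has one value at week 0 and another at week 12. A paired t-test on FC therefore estimates the true FC change plus whatever FC change comes from the motion change. It has no concurrent control to absorb the second part. A second scan may be stiller simply because it is familiar.

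Two later steps depend on these maps. The conjunction analysis uses the within-arm treatment effects. The FC–symptom correlation is computed within VA only, where randomisation gives no protection: a patient who becomes less anxious or sleeps better may also lie stiller, and motion could then produce a link between FC and symptoms.

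**Working it through.** **The plan's own figure.** The sample size section gives 21 per group by a rule of thumb, with no effect size, SD or power, so there is no formula to reproduce. The count agrees with the recruitment target: 42/2 = 21 per arm, and 42 + 21 = 63 in total.

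**Inputs.**
- n = 21 per arm (Sample size calculation).
- Two-sided 5% for a single voxel or region. The 5% is from MRI data preprocessing; two-sidedness is assumed.
- r = correlation between FC change and FD change that remains after preprocessing (assumed).
- d = mean FD change in SDs of FD change; for VA versus SA, the between-arm difference in mean FD change on that scale (assumed).
- No true FC change.

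**Within-arm paired test.** The standardised mean FC change caused by motion is r × d. The paired t statistic is noncentral t with 20 df and noncentrality r × d × √21. For r = 0.4 and d = 0.5 this is 0.4 × 0.5 × 4.583 = 0.917, and the rejection rate is 14.1%.

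| r | d | noncentrality | rejection rate |
|---|---|---|---|
| any | 0 | 0 | 5.0% |
| 0 | any | 0 | 5.0% |
| 0.2 | 0.3 | 0.275 | 5.8% |
| 0.2 | 0.5 | 0.458 | 7.2% |
| 0.3 | 0.5 | 0.687 | 10.0% |
| 0.4 | 0.5 | 0.917 | 14.1% |
| 0.5 | 0.5 | 1.146 | 19.4% |
| 0.3 | 0.8 | 1.100 | 18.2% |

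**VA versus SA.** With two groups and two visits, the group-by-time F test equals the two-sample t-test on change scores. Its noncentrality is r × d × √(21/2) = r × d × √10.5, with 40 df, where d is the between-arm difference. A shift shared by both arms gives d = 0, hence 5%. If the arms do differ:
- r = 0.3, d = 0.5: 7.6%
- r = 0.5, d = 0.5: 12.4%
- r = 0.4, d = 0.8: 17.3%

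**Simulation check.** 20,000 simulated trials per cell, 21 per arm, r of 0, 0.2 and 0.4, mean shift of 0, 0.25, 0.5 and 1.0 SD:
- Paired test, r = 0.4, shift 0.5: 0.143 (14.1% above). For r = 0.2, shift 0.5: 0.071 (7.2% above).
- VA–SA with the same shift in both arms: 0.047 to 0.052 in every cell, however large the shift.
- VA–SA with the shift in one arm only, r = 0.4, shift 0.5: 0.099 (9.7% by formula).
- With FD change as covariate: 0.047 to 0.053 for all tests in all cells.

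**The case against.** **Silence in a condensed article.** The article never states that the longitudinal models are unadjusted, and covariate lists are often left to a fuller document. That is a fair caution. However, the section does set group-level covariates for one FC comparison and then names the longitudinal models without any. An analyst following the text would fit them unadjusted.

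**The asymmetry has a reason.** DOR versus HC is not randomised, whereas VA versus SA is. This stands for the VA–SA map. It does not help the within-arm maps, which compare nothing randomised.

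**A stronger reading.** A reader might infer that all the longitudinal tests respond to motion instead of to acupuncture. The documents do not support that. Every test still responds to a true FC change; motion adds a second route to rejection, and only if a motion–FC link survives preprocessing. In the VA–SA comparison a common shift, such as familiarity with the scanner, cancels.

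**Adjustment can do harm.** If acupuncture reduces anxiety and that reduces motion, FD change is a consequence of treatment. Conditioning on it could remove part of the effect or introduce bias. This also stands, and is why FD adjustment should not be primary for VA versus SA.

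**The size is assumed.** Nothing in the documents informs r or d. The rates are for single uncorrected tests, not the plan's map-level error after voxel, cluster and FDR thresholds. A common shift would also tend to show in both the VA and SA maps, where a careful reader could notice it. These points limit the size but do not remove the problem.

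**Conclusion.** The concern holds for the within-arm pre/post maps and for what is built on them, the conjunction analysis and the VA-only correlation. It holds for VA versus SA only on the condition that motion change differs by arm.

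For assumed r of 0.2 to 0.5 and d of 0.3 to 0.5, the per-test false-positive rate of the paired analysis is about 6% to 19% against a nominal 5%. The low end is negligible, and there is no inflation if r or d is zero. These figures illustrate sensitivity and do not estimate what will happen in this trial. The study calls itself exploratory, which lowers the stakes. The change is still worth making before the maps are seen, because these maps carry the mechanistic conclusion.

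**What to change.** In the longitudinal part of MRI data preprocessing, and in the paragraph on conjunction and correlation analyses that follows it:

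1. **Within-arm maps:** model FC change with the change in scan-level mean FD as covariate, and test the intercept at zero FD change. Show the unadjusted maps alongside.
2. **FC–symptom correlations in VA:** partial out FD change.
3. **VA versus SA:** keep the randomised group-by-time comparison as primary, and add an FD-change-adjusted map as a sensitivity analysis.
4. **Reporting:** give mean FD by arm and visit, so that readers can see whether motion shifted and whether it shifted differently by arm.

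The cost is a few lines of analysis text and one degree of freedom per adjusted model; mean FD is already needed for the DOR–HC map. The downside is that adjustment may remove some real effect if lower motion is itself a result of treatment. The unadjusted within-arm maps cover that.

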### Participants

We plan to recruit 42 patients with DOR and 21 healthy female volunteers of childbearing age through WeChat, poster postings, and other channels. A dedicated staff member will be responsible for patient recruitment and will meticulously record each participant’s information, which will be documented in the Case Report Form (CRF). The recruitment materials will include detailed contact information. This study adheres to the principles outlined in the Declaration of Helsinki.

Inclusion criteria for healthy controls:

Age between 20 and 40 years (inclusive).Normal gynecological ultrasound, normal hormone levels, and regular menstrual flow with normal color and quantity.No severe heart, liver, kidney, or hematologic system disorders.Right-handed.Voluntary participation in the trial and signed informed consent.

The inclusion criteria for DOR are similar to our previous design (23):

Age between 20 and 40 years (inclusive).Diagnosis of DOR based on the 2016 POSEIDON criteria and the 2020 expert consensus on the treatment of low-prognosis populations in assisted reproductive technology using the Delphi method in China.AMH level < 1.2 ng/ml.AFC < 5 (Note: AFC should be measured on days 2–3 of the menstrual cycle, with at least a 4-week interval between two measurements).Fertility desire, with plans for natural conception or, as assessed by a reproductive specialist, plans to undergo controlled ovarian stimulation with an antagonist protocol in the next *in vitro* fertilization (IVF) and embryo transfer cycle.Right-handed.Voluntary participation in the trial and signed informed consent.

Exclusion criteria:

Coexisting conditions that affect fertility, including congenital reproductive organ abnormalities, untreated endometrial polyps, untreated uterine infections, untreated tubal hydrosalpinx, thin endometrium, uterine fibroids, endometriosis, or other organic diseases.Coexisting polycystic ovary syndrome (PCOS).Coexisting untreated hyperprolactinemia, hyperandrogenism, thyroid dysfunction, chronic adrenal insufficiency, or other metabolic and endocrine disorders.Acupuncture treatment for fertility enhancement received within the last three months.Plans for *in vitro* fertilization (IVF-ET) within 2 months after enrollment.Vulnerable populations other than illiterate individuals, including those with mental illness, cognitive impairments, critically ill patients, pregnant women, etc.

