### Sample size calculation

This is an exploratory study, and according to the highly cited experimental fMRI studies had a single group of participants and these studies had median sample size of 12, the sample size of 12 cases in each group and 20 to 30 cases has become the “minimum requirement” and most choices for acupuncture imaging confirmatory studies. We have expanded the sample size to 21 cases per group (36).

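### The conjunction reuses the DOR baseline scans in both maps, which tilts it toward apparent normalisation in either arm; neither it nor the VA-only correlation can show an acupuncture-specific mechanism

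*Protocol article*

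**What the plan says.** All places are in the protocol article.

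- **Scans** (fMRI data acquisition). For patients: "All DOR patients received two separate resting-state fMRI scanning, before and after the 12 weeks acupuncture treatment course". For controls: "The healthy controls participated only in one resting-state scanning as baseline control".
- **Disease map** (MRI data preprocessing): "Two-sample t-tests will be conducted to identify significant differences in FC between the DOR and healthy control (HC) groups".
- **Treatment maps** (same section): paired t-tests within each arm, and a two-way ANOVA between arms.
- **Conjunction** (end of the same section). Its purpose is to learn whether the altered hypothalamic connectivity of DOR patients responds to acupuncture. It will "compare the FC change maps in DOR patients with the treatment effects observed in the VA and SA groups, respectively".
- **Correlation** (same place): between the "significantly altered hypothalamus-related FCs and the corresponding clinical improvements in the VA group".

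Study design gives the use of these results: to investigate whether acupuncture changes hypothalamic connectivity and thereby improves symptoms.

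**The concern.** Controls have a single scan and the DOR-HC comparison is the cross-sectional experiment, so the disease map is DOR baseline minus HC. Each arm's treatment map subtracts that same baseline from the post-treatment scan. A connection that is high at baseline by chance looks abnormal in the first map and tends to fall in the second. This is regression to the mean built into the comparison, and it looks like recovery.

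The conjunction is also done one arm at a time, with no test of whether the overlap in VA exceeds that in SA. The FC-clinical correlation leaves out the sham arm, so a link produced by time, expectation or repeat scanning would look the same as one produced by needling. At stake is the mechanistic conclusion drawn from these two follow-on analyses.

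**Working it through.** The plan gives no error rate or power for these analyses, so there is no figure to reproduce beyond the group sizes.

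**Inputs from the article**
- Participants: "We plan to recruit 42 patients with DOR and 21 healthy female volunteers of childbearing age".
- Acupuncture interventions: "randomly allocated into the VA or SA group at a 1:1 ratio".
- Sample size calculation: "We have expanded the sample size to 21 cases per group". Hence 2 x 21 = 42 DOR and 21 HC, which agrees.

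**Assumptions**
- Equal variance s² in all groups and at both scans.
- Scan-rescan correlation rho, which the article does not give; shown from 0 to 0.9.
- Two-sided 0.05 per voxel.
- No disease effect and no treatment effect.

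**Null correlation of the two maps**
- A = mean baseline FC of 42 DOR - mean of 21 HC. Var(A) = s²(1/42 + 1/21) = s²/14.
- B = mean of (post - baseline) in the 21 VA patients. Var(B) = 2s²(1 - rho)/21.
- VA patients carry weight 21/42 in A, so Cov(A,B) = -(21/42) x s²(1 - rho)/21 = -s²(1 - rho)/42.
- Corr(A,B) = -[(1 - rho)/42] / sqrt[(1/14) x 2(1 - rho)/21] = -0.289 x sqrt(1 - rho).

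**Consequence for a voxel falsely called altered** (bivariate normal, both tests at 0.05; 2.5% in each direction if the maps were independent)

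| rho | Corr | Toward normal | Away | Ratio |
|---|---|---|---|---|
| 0 | -0.29 | 9.1% | 0.3% | 30 |
| 0.3 | -0.24 | 7.6% | 0.5% | 16 |
| 0.5 | -0.20 | 6.5% | 0.65% | 10 |
| 0.7 | -0.16 | 5.4% | 0.9% | 6 |
| 0.9 | -0.09 | 4.0% | 1.5% | 2.7 |

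Simulating the actual t-tests (400,000 null voxels per rho) gives a slightly milder tilt. At rho 0.5, 6.2% go toward and 0.8% away in VA, about 7.5 to 1. In SA, 6.4% go toward. The bias is the same in both arms, within simulation error.

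**The VA-SA contrast**
- SA has the same covariance with A, so Cov(A, B_VA - B_SA) = -s²(1 - rho)/42 + s²(1 - rho)/42 = 0.
- The same cancellation holds for post-treatment FC adjusted for baseline with a common slope b: each arm contributes s²(rho - b)/42, and the difference is zero.
- Simulated for change scores, the correlation with A is 0.00. Given a falsely altered voxel, 2.5% to 2.65% are significant in each direction, close to the nominal 2.5%.

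**The correlation**
- In VA alone (n = 21), |r| must reach 0.43 for p < 0.05, and r of about 0.58 is needed for 80% power.
- For VA against SA on Fisher's z, SE = sqrt(2/18) = 0.333. If r = 0 in SA, VA needs tanh(1.96 x 0.333) = 0.57 for significance and tanh(0.934) = 0.73 for 80% power.

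**The case against.** The strongest reply is that the plan already tests specificity. MRI data preprocessing has a between-arm ANOVA of the FC maps, and Study design has a VA-SA comparison of FC and symptoms. This stands. A reader might infer from the conjunction that specificity is never tested or that the randomised contrast goes unused; the article does not support either statement. The ANOVA does not, however, ask whether connections altered in DOR are the ones that VA shifts more than SA, nor whether FC change tracks clinical change differently by arm.

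A reader might also infer that the artefact favours verum over sham. It does not, being equal in both arms. Nor does the single HC scan make retest drift inseparable from a treatment effect: the SA arm is scanned twice and serves as a concurrent retest control. The arm-by-arm conjunction simply does not use it that way. The article also states no rule that overlap in VA without overlap in SA counts as a difference, so that misuse is a risk and not a plan.

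The magnitudes have limits. They are conditional on a false DOR-HC finding. At rho 0.5 the joint per-voxel rate is only 0.05 x 6.5% = about 0.3%. The planned cluster and FDR correction would lower the absolute rates, though it does not remove the asymmetry of sign. A real DOR-HC difference would reduce the share of voxels selected by chance.

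Finally, Sample size calculation calls the study exploratory, and the correlation is described as examining a relationship, not as proving specificity. That lowers the severity. It excuses low power, but not a directional bias that can be removed.

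**Conclusion.** The concern holds in a limited form. Shared baseline scans give the disease map and each arm's change map a null correlation of -0.289 x sqrt(1 - rho). At assumed rho of 0.3 to 0.7, about 5-8% of falsely altered voxels appear to normalise, against 2.5% expected, and under 1% move away. The direction is the same across rho from 0 to 0.9; the ratio runs from about 30 down to 2.7. These figures assume no true DOR-HC difference and are per voxel before correction.

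Overlap within a single arm is therefore not evidence that acupuncture normalises connectivity, and a VA-only correlation cannot attribute the FC-clinical link to acupuncture. The planned between-arm ANOVA is unaffected by the coupling. This is a should-fix for an exploratory follow-on analysis; it does not invalidate the randomised comparison.

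**What to change.** 1. Use the DOR-HC map only as a mask. Within it, test VA against SA on post-treatment FC, adjusted for baseline FC, the age stratum used in randomisation and mean FD.
2. Report the separate-arm conjunctions as descriptive only, and say that the shared baseline tilts both toward apparent normalisation.
3. Run the FC-clinical association in all DOR patients: outcome change on FC change, group, group x FC change and baseline values. Claim specificity only from the interaction.

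The cost is analysis wording; the planned scans and outcomes suffice. The price is fewer positive mechanistic findings and an interaction with low power: on the Fisher z approximation above, only a strong VA correlation beside a null SA correlation would be detected. Statements about specificity should be correspondingly modest.
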